### Tertiary outcomes

1. Difference in haemorrhage size and location results provided by e-ASPECTS versus expert human readers.2. Potential clinical impact of e-ASPECTS and e-CTA on routine acute stroke care, whether: a. knowledge of ASPECTS conveyed using e-ASPECTS visual overlay on imaging influences diagnostic confidence or alters treatment decisions,b. use of e-ASPECTS/e-CTA alter the time required for scan interpretation, andc. e-ASPECTS or e-CTA results are associated with outcome after ischaemic stroke.

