### Tertiary outcomes

**
*1. Haemorrhage quantification by e-ASPECTS versus expert human readers.*
** We will use all RITeS NECT containing acute haemorrhage for this analysis. This includes scans acquired from haemorrhagic stroke trials (i.e. brain haemorrhages with or without intraventricular extension) in addition to scans classed as mimics in ischaemic stroke trials (e.g. subdural or subarachnoid haemorrhages).

Haemorrhage will be quantified by location and extent as follows.

*Haemorrhage location*

Haemorrhage location will be defined by side and gross anatomical regions of the brain affected including cerebral lobes (i.e. frontal, parietal, temporal, occipital), basal ganglia, brainstem, cerebellum, or extra-axial compartment (i.e. intra-ventricular, subarachnoid, subdural, extra-dural). We will convert e-ASPECTS haemorrhage detection overlay to these same 22 (11 per side) categories following visual review, blinded to human-reader results.

We will look at differences in the regions (and their number) identified by expert humans and e-ASPECTS and if the data are amenable, consider using methods that account for multiple concurrent haemorrhage sites per patient^52^.

*Haemorrhage extent*

Haemorrhage extent will require a comparison of haemorrhage volume calculated at the voxel level (e-ASPECTS) and haemorrhage dimensions used to estimate volume (i.e. the ABC/2 score^21^,^53^, human readers). We will use Bland-Altman testing (expected range of agreement to be within ± 10 mm^3^) and K-alpha statistics to test agreement between e-ASPECTS and human-rated results.

**
*2a. Impact of e-ASPECTS on diagnostic confidence and treatment decisions.*
** We will invite stroke and hospital admission physicians with a range of experience to complete an online questionnaire including RITeS NECT and relevant clinical scenarios, similar to previous work conducted by RITeS members^1^,^54^. We will compare responses for readers before and after ASPECTS is calculated (i.e. with and without e-ASPECTS overlay) to assess whether ASPECTS alters confidence in stroke diagnosis and determine its influence on management decisions.

RITeS cases with the following range of relevant radiological findings will be selected: with obvious, subtle and no ischaemic brain lesions (and a range of ASPECTS results); with and without hyperattenuating arteries; with subtle brain and extra-axial haemorrhage; with and without pre-stroke brain changes.

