The questionnaire will contain 24 cases including some repetition of the same NECT with and without e-ASPECTS overlay. Specifically, we will include 10 cases shown with and also without e-ASPECTS overlay. To limit reader recognition of repeat cases, these images will be modified (e.g. left-right reversal, removal of any visible extracranial image components) and presented in a non-sequential order. We will also include two unique cases with and two unique cases without e-ASPECTS overlay; each of these 4 cases will be displayed only once. Thus 12 cases will be presented with and 12 without e-ASPECTS overlay. A unique clinical history will be provided for all 24 cases but we will limit clinical variability between repeat cases with and without e-ASPECTS overlay. Each case will include a panel of JPEG images representing the whole brain. Repeat images with and without e-ASPECTS overlay will include identical slices.

We will include up to three questions for each case:

1. Is the e-ASPECTS overlay helpful?• Yes• No2. Given the clinical history and the images presented, would you• Treat the patient immediately with IV alteplase (+/- refer for thrombectomy where available)• Refer the patient immediately for thrombectomy without IV alteplase• Not treat the patient with IV alteplase or thrombectomy but transfer to the acute stroke ward• I’m not sure, I’d first ask for a neuroradiology opinion• I’m not sure, I’d like to do more imaging such as angiography, perfusion imaging or MRI (not available here)3. How confident are you with this decision?• Very unsure• Unsure• Sure• Very sure

We will present these results as per Table 9, and visually in bar charts. We will compare results for the following subgroups in univariable analysis (chi-squared statistics): with versus without e-ASPECTS overlay, more versus less experienced readers, obvious versus subtle or no ischaemic lesion, with versus without haemorrhage, with versus without hyperattenuated arteries, with versus without leukoaraiosis, atrophy or old stroke lesions.

**
*2b. Use of e-ASPECTS/e-CTA and time required for scan interpretation.*

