**TOTAL**			

**Note:** All results n (%). Proximal = ICA or proximal MCA (M1). Distal = distal MCA (M2+).

**Table 7. T7:** Options for comparing modified Tan (e-CTA) and Miteff methods (human rated) of MCA collateral scoring.

Modified Tan used by e-CTA to grade collaterals	Miteff comparison 1	Miteff comparison 2	Miteff comparison 3
3 = Excellent (>90%)	Good	Good	Good
2 = Good (50–90%)		Moderate	Moderate
1 = Poor (10–50%)	Moderate		Poor
0 = None (0–10%)	Poor	Poor	

**Table 8. T8:** Planned results for e-ASPECTS and e-CTA repeatability testing.

Tested Component	Result
e-ASPECTS, ischaemia	N, % with matched ASPECTS results
	N, % for each of 1–10 point ASPECTS difference
	Median, IQR for difference in scores
e-ASPECTS, haemorrhage	N, % with matched location results
	N, % for each of 22 named regions
	Median, IQR for comparison of haemorrhage volumes
e-CTA, obstruction	N, % with matched ICA-MCA proximal vs distal results
e-CTA, collateral scoring	N, % with matched collateral scores
	Median, IQR for comparison of collateral scores

Note: ICA = internal carotid artery. MCA = middle cerebral artery.

**Table 9. T9:** Planned results for effect of e-ASPECTS on diagnostic confidence and treatment decisions questionnaire.

Question	Total, n (%)	Subgroups: e-ASPECTS overlay, reader experience, visible ischaemic lesion, haemorrhage, hyperattenuating arteries, leukoaraiosis, atrophy, old stroke lesions		Absolute differences, 95% CI and p-value
		With n (%)	Without n (%)	
Found e-ASPECTS overlay helpful				
Decision				
Treat patient with thrombolysis/ thrombectomy				
No acute treatment				
Request further radiological input				
Confidence in decision				
Very unsure				
Unsure				
Sure				
Very sure				

Note: Table truncated for presentation of subgroups.

**Table 10. T10:** Planned ordinal regression analysis results with 3–6-month post-stroke outcome as dependent variable.

Variable	Raw Data N (%) or Median (IQR)	Odds Ratio, OR	95% Confidence Interval	p-value
Age, years				
NIHSS				
Time from stroke onset, minutes				
Treated with alteplase +/- thrombectomy				
Software-derived result *				

Note: NIHSS = National Institutes of Health Stroke Scale, IQR = Inter-quartile range. * Either ASPECTS result, presence/absence of ICA-MCA axis occlusion, MCA collateral score.

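### Tertiary outcome 2a is named diagnostic confidence, but the questionnaire measures only confidence in the management choice, pooled over definite and not-sure answers

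*SAP article*

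**What the plan says.** In the Methods of the SAP article, Tertiary outcomes item 2a asks whether knowledge of ASPECTS, shown as the software overlay, "influences diagnostic confidence or alters treatment decisions". The Statistical analysis section, under Tertiary outcomes 2a, restates the aim: responses with and without the overlay are compared to "assess whether ASPECTS alters confidence in stroke diagnosis and determine its influence on management decisions". Both statements name two constructs, one about diagnosis and one about management.

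The instrument is then printed in full. It is introduced with "We will include up to three questions for each case", and the questions are:

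1. "Is the e-ASPECTS overlay helpful", answered yes or no.
2. "Given the clinical history and the images presented, would you", followed by five management options. Three are definite choices. The other two open with a declaration of uncertainty, one leading to a neuroradiology opinion and the other to more imaging.
3. "How confident are you with this decision", on four levels from very unsure to very sure.

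The title of Table 9 presents the results as the effect on diagnostic confidence and treatment decisions. Its confidence block is headed "Confidence in decision" and is shown beside, not within, the decision categories. Comparisons are univariable chi-squared tests, with versus without overlay among them.

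**The concern.** The construct in the outcome is not the construct in the questionnaire. A reader may be certain that a scan shows ischaemic stroke and unsure whether to treat, or the reverse. The management choice also draws on the clinical history, which question 2 invokes explicitly. Each of the 24 presentations has its own history, and differences between repeated cases are to be limited, not removed. Management confidence can therefore differ between the two showings of one scan for reasons unrelated to what the reader thinks the scan shows.

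A second, smaller problem follows from question 3 being asked after every option. A very sure answer after a definite choice and a very sure answer after a not-sure option mean different things, yet both enter the same row of Table 9. At stake is a published statement that the overlay raises or lowers diagnostic confidence, based on data that do not measure it. Analysis cannot recover the missing construct once responses are in.

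**Working it through.** The plan gives no figure to reproduce. The check sets the stated outcome against the items and the table shell.

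**Outcome against items**

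| Construct named in outcome 2a | Item that measures it | Place in Table 9 |
|---|---|---|
| Treatment decision | Question 2 | Decision rows |
| Confidence in stroke diagnosis | None | Named in the title only |
| Confidence in the management choice (not named in 2a) | Question 3 | Confidence block |

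Question 1 concerns helpfulness. Question 2 asks for an action. The decision referred to in question 3 can only be the answer to question 2. So none of the three items asks directly about diagnostic confidence.

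**Does a skip rule remove the second problem?** The wording allows fewer than three questions per case. The natural reason is that question 1 makes no sense for the 12 presentations without an overlay. No rule is stated that drops question 3 after a not-sure answer.

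**Can the pooled scale move against certainty?** Take one reader and one repeated case:

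- Without overlay: not sure, would ask neuroradiology; confidence very sure (level 4 of 4).
- With overlay: a definite decision to treat; confidence sure (level 3 of 4).

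This reader has gone from declared uncertainty to a definite decision, while the confidence score falls from 4 to 3.

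**Bounds for the pooled share.** Suppose, as an assumption, that the overlay moves 10% of responses between the definite and the not-sure options and leaves all other ratings unchanged. Each moved response changes the indicator for sure or very sure by −1, 0 or +1. The pooled share then changes by between 10% × (−1) = −10 percentage points and 10% × (+1) = +10 points. The +10 end needs every mover to pass from an unsure rating to a sure one; the −10 end needs the opposite. The direction of the shift between options does not fix the sign of the change in pooled confidence. Only a cross-tabulation of confidence by decision would show which case applies.

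**The case against.** Several points can fairly be made for the plan.

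- **Half of 2a is measured directly.** Question 2 captures treatment decisions. That stands: a reader might infer that outcome 2a cannot be reported at all, and the plan does not support this.
- **The management choice carries some diagnostic information.** Choosing thrombolysis or thrombectomy implies a belief in ischaemic stroke. That stands too. Question 3 is an imperfect proxy and not an empty one, but a proxy should not carry the name of the construct.
- **The scale has a clear direction.** A reader might infer that the confidence scale is broken. It is not. It is clear after the three definite options, and after a not-sure option it can be read coherently as confidence in the choice to seek help. The difficulty arises only when pooled answers are read as certainty.
- **Table 9 already shows a shift towards asking for help.** Its row for further radiological input gives the net change, with an absolute difference and confidence interval. The shift is therefore not hidden. What is absent is how confidence was rated within each decision.
- **Two of five options is not 40% of responses.** That counts answer choices. The plan gives no expected frequency for them.
- **Reach is small.** This is part of one tertiary outcome, to be reported after the primary publication.

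**Conclusion.** The mismatch is real. The outcome and the title of Table 9 name diagnostic confidence, while the only confidence item measures confidence in the management choice. Followed as written, the plan supports at most an indirect inference about diagnostic confidence. Separately, the pooled confidence comparison with and without overlay cannot be read as a change in certainty, because question 3 also follows two not-sure options and is not cross-classified by decision.

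The effect on results cannot be sized from the document. The ±10 points above are bounds under an assumed 10% shift and not a forecast. The conclusion rests on two readings: that the decision in question 3 is the answer to question 2, and that no unstated skip rule applies after a not-sure answer. The first is hardly open to doubt. If the second were wrong, only the pooling problem would fall away. No primary or secondary outcome is touched. The change is worth making because, according to Dissemination of results, the data for tertiary outcomes still have to be collected.

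**What to change.** Before the questionnaire opens, add one item per case asking for the most likely diagnosis (for example ischaemic stroke, haemorrhage, mimic, no acute cause), with confidence in it on the same four levels as question 3. Use that item for the diagnostic-confidence outcome and give it its own block in Table 9. If it is not added, rename the outcome and the title of Table 9 as confidence in the management decision.

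In either case, report question 3 cross-tabulated by question 2 category, over all responses, with and without overlay.

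Two tempting alternatives are best avoided. Restricting the confidence analysis to definite answers conditions on a response that the overlay may itself change, and it would lose some of the 10 repeated pairs. Ranking the not-sure options below very unsure merges choice and confidence into an ad hoc scale and scores asking for help as the worst answer.

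The cost is a slightly longer questionnaire: one more item for each of 24 presentations per reader, and a larger table. No extra readers are needed.

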### 2c. Association between e-ASPECTS or e-CTA results and clinical outcome after stroke

We will use the entire RITeS samples of NECT and CTA for these analyses but also perform sensitivity analyses using the representative NECT sample.

In separate multivariable analyses, we will test whether the three main software outputs of e-ASPECTS (ASPECTS result) and e-CTA (ICA-MCA axis occlusion, MCA territory collateral score) are independently associated with stroke outcome. We will include the following variables in each model since these are already known to be associated with outcome after stroke: age, NIHSS, time from stroke onset, treatment with alteplase and/or thrombectomy (vs no treatment). The dependent variable in each model will be functional outcome after stroke. Assessment of functional outcome after stroke varies among the RITeS trials and includes either the modified Rankin Score (mRS) at 90 days, or the Oxford Handicap Scale (OHS) at 6 months from stroke onset. Both mRS and OHS are 7-point scalar ranging from normal (0) through increasing disability (1–5), to death (6). We will use multivariable ordinal logistic regression to calculate common odds ratios for good outcome, presented as per Table 10.

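### The ordered four-level confidence answer is compared only by chi-squared, which ignores the order, gives no single estimate of direction and usually loses power for a shift

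*SAP article*

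**What the plan says.** Item 2a of the Tertiary outcomes describes an online questionnaire for physicians, meant "to assess whether ASPECTS alters confidence in stroke diagnosis and determine its influence on management decisions". Question 3 reads "How confident are you with this decision?• Very unsure• Unsure• Sure• Very sure". On layout the SAP article states: "Thus 12 cases will be presented with and 12 without e-ASPECTS overlay". On repeats it states: "Specifically, we will include 10 cases shown with and also without e-ASPECTS overlay".

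The only analysis method named for the answers is this: "We will compare results for the following subgroups in univariable analysis (chi-squared statistics"). It covers overlay versus no overlay, reader experience and the radiological subgroups alike. Table 9 ("Planned results for effect of e-ASPECTS on diagnostic confidence and treatment decisions questionnaire") lists the four confidence levels as separate rows of n (%), with one column for absolute difference, 95% CI and p-value. Bar charts are also planned.

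No trend test, rank test or ordinal model is named for this item. Elsewhere the plan does respect order. Section 2c says of functional outcome: "We will use multivariable ordinal logistic regression to calculate common odds ratios for good outcome". The absolute ASPECTS difference (Secondary outcomes, item 1) also gets ordinal logistic regression, and scalar repeatability results get Mann-Whitney tests.

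**The concern.** The four answers form a scale, and a natural reading of the aim is whether the overlay makes readers more or less sure. Pearson chi-squared treats the answers as unordered labels: shuffle the four columns and the statistic and p-value stay the same. A significant result therefore does not itself say that confidence rose, fell or spread, and the test supplies no one-number effect with a confidence interval. Its 3 degrees of freedom also dilute power when the true effect is a shift in one direction. A real change in confidence could be missed, or be reported as a bare p-value beside four rows that the reader must interpret.

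**Working it through.** **Inputs from the SAP article.** Four ordered answers; 12 readings per reader with the overlay and 12 without; 10 cases shown both ways plus 4 shown once (10 x 2 + 4 = 24 readings of 14 distinct cases).

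**Inputs assumed, because the plan gives none.** Two-sided 5%; 5 to 30 readers (12 x 5 = 60 up to 12 x 30 = 360 readings per arm); common odds ratio 1.3, 1.5 or 2.0; baseline answers 10/30/45/15%. The plan has no power figure for this outcome, so there is none to reproduce.

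**Step 1: order.** The statistic is X² = sum of (O − E)²/E over the 2x4 cells, with (2 − 1)(4 − 1) = 3 df. A sum over cells does not change when the columns are permuted, so order plays no part.

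**Step 2: asymptotic loss.** At non-centrality λ, power with k df is 1 − F(c_k; k, λ), where F is the non-central chi-squared distribution function and c_k the 95% point of the central one. Giving both tests the same λ:

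| λ | Ordered test, 1 df | Chi-squared, 3 df | Loss (points) |
|---|---|---|---|
| 0.43 | 10% | 7.6% | 2.4 |
| 2.06 | 30% | 19.7% | 10.3 |
| 3.84 | 50% | 34.5% | 15.5 |
| 6.17 | 70% | 53.1% | 16.9 |
| 7.85 | 80% | 64.5% | 15.5 |
| 10.51 | 90% | 78.4% | 11.6 |
| 12.99 | 95% | 87.1% | 7.9 |
| 16.11 | 98% | 93.6% | 4.4 |

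Interpolating between 90% and 95%, the loss passes 10 points at about 90 + 5 x (11.6 − 10)/(11.6 − 7.9) = 92%.

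**Step 3: simulation with the plan's layout.** The shift divides each cumulative odds by the odds ratio. For OR 1.5 the cumulative proportions 0.10, 0.40, 0.85 have odds 0.111, 0.667, 5.667. Divided by 1.5 these are 0.074, 0.444, 3.778, giving 0.069, 0.308, 0.791, so the answers become 6.9/23.9/48.3/20.9%. Power of chi-squared versus a tie-corrected Mann-Whitney test, 20,000 runs each, readings independent:

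| Readers (per arm) | OR 1.3 | OR 1.5 | OR 2.0 |
|---|---|---|---|
| 5 (60) | 8.5 vs 12.0% | 14.6 vs 21.9% | 35.6 vs 52.5% |
| 10 (120) | 13.3 vs 19.9% | 26.1 vs 39.1% | 66.2 vs 81.6% |
| 20 (240) | 22.1 vs 33.9% | 49.2 vs 66.5% | 94.2 vs 98.3% |
| 30 (360) | 33.2 vs 48.1% | 68.9 vs 83.6% | 99.3 vs 99.9% |

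The largest loss is about 17 points. The smallest are about 4 points with 5 readers at OR 1.3, and under 1 point with 30 readers at OR 2.0. Uniform and skewed baselines (25% each; 5/15/45/35%) give the same pattern.

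**Step 4: the opposite pattern.** If answers spread from 10/40/40/10% to 20/30/30/20% with 120 per arm, chi-squared has 83% power and the rank test 5%.

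**Step 5: repeated readers and cases.** With 20 readers and reader and case effects of SD 1 each on the logit scale (assumed), chi-squared versus rank test gives 46% vs 61% at a log odds ratio of 0.5 and 74% vs 86% at 0.7. Under no effect the rejection rates are 6.1% and 8.2% for overlay, and about 32% and 37% for reader experience. Neither pooled test holds 5%, so an ordered test alone is not a full remedy.

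**The case against.** **The 3-df test is inferred.** The plan gives no table shape. Table 9's difference column would fit four row-by-row 2x2 tests at least as well, and then the 80% versus 64.5% comparison does not apply as computed. This stands as an ambiguity, but row-by-row tests also ignore order and give four p-values for one question. A chi-squared test for trend would meet the concern, but none is named.

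**Direction is visible anyway.** A reader might infer that the plan hides whether confidence rose or fell. It does not: the Table 9 rows and the bar charts would show it. What is missing is a test and a single estimate aimed at direction.

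**The aim is whether confidence alters, without a stated direction.** A spread to both extremes is an alteration, and chi-squared detects it far better (step 4). This stands, and the power loss must be stated as conditional on a shift.

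**Stronger claims a reader might infer.**
- That the loss is an unconditional 10 to 20 points. With no reader number or effect size in the plan this cannot be said, and no setting exceeded about 17.
- That the loss drops below 5 points only near 100% power. It does so at very low power too (5 readers, OR 1.3).
- That all the plan's other ordered outcomes get ordinal regression. Only the ASPECTS difference and functional outcome do. Collateral scores use K-alpha, and the direct ASPECTS comparison uses rank tests, Bland-Altman plots and K-alpha.

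**The outcome is minor.** It is tertiary, reported separately, and carries no power claim. That limits the consequence.

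**Conclusion.** The point holds as a cheap improvement to a tertiary outcome. The named method does not use the order of the confidence scale and gives no single directional estimate; that follows from the text on its plain reading and needs no assumption. The size of the power loss does need assumptions: two-sided 5%, a one-direction proportional-odds shift and a 3-df Pearson test. Under these it is about 10 to 17 points where an ordered test would have about 30% to 92% power, and less outside that range. The documents do not support the inference that the planned comparison would fail or mislead. It is less efficient and less informative for the effect most readers will look for.

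**What to change.** In item 2a, state that question 3 will be analysed on its full ordered scale with a proportional-odds (cumulative logit) model that includes random effects for reader and case. Report one common odds ratio with 95% CI for overlay versus no overlay and for each listed subgroup factor. Keep the four confidence rows of Table 9 as description, which would also show any spread to the extremes, and take the confidence item out of the chi-squared statement.

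The reader and case effects are needed because each reader answers all 24 items and 10 cases appear twice; a plain proportional-odds model would carry over the excess rejection in step 5.

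The cost is SAP wording and no new data. The proportional-odds assumption must be checked, and the mixed model is slightly more work. With only 14 distinct cases, intervals for case-level factors may be wide.

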** We will select 100 NECT and 50 CTA from all RITeS cases that have been successfully processed by e-ASPECTS or e-CTA software, respectively and where expert human and software results match (to limit the likelihood that one test group is disadvantaged by known or unknown factors that make scan reading more difficult for either group). We will use stratified random sampling to ensure relevant scan appearances are equally represented as follows: From all available NECT with valid e-ASPECTS result we will create three stratai. No acute ischaemic lesion (i.e. ASPECTS = 10)ii. Small acute ischaemic lesion (ASPECTS 6-9)iii. Medium-large acute ischaemic lesion (ASPECTS 0-5)From all available CTA with valid e-CTA result we will create three stratai. No arterial obstructionii. Proximal ICA-MCA obstructioniii. Distal MCA obstruction

We will randomly sample similar numbers (i.e. one-third) from each of the three NECT and CTA strata (therefore ~33 cases for each NECT stratum and ~16 for each CTA stratum).

We will examine the performance of e-ASPECTS/e-CTA software versus: a. Radiology/stroke physician trainees, front-of-house clinicians (non-experts)b. Experienced stroke physicians or neuroradiologists (experts)

We aim to include a minimum of five expert and five non-expert readers. Each reader will be shown a unique random 10% selection (10 NECT and 5 CTA) of the cases on a PACS (picture archiving and communication system) workstation suitable for clinical review of DICOM imaging. If more than 10 readers are recruited to the study, we will allow repeat reading of cases. Readers will be asked to fully evaluate CT and CTA as required for routine stroke care using a standard proforma. Full evaluation will include assessment for all potential causes of stroke symptoms in any intracranial location (NECT – ischaemic brain lesion including ASPECT scoring, hyperattenuating artery sign, haemorrhage, mass lesion) and identification of arterial obstruction that might cause ischaemic stroke (CTA – including collateral scoring when relevant). All scan ratings will be performed blind to clinical characteristics, prior human reading and prior e-ASPECTS/e-CTA software results.

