An observer will record the time taken (in seconds) for full NECT and CTA evaluation, as well as the time needed for ASPECT and CTA obstruction scoring alone. Software times will be measured from initiation of the software prior to scan loading to receipt of a valid output. Valid outputs include either an ASPECT score, identification of a hyperattenuated artery, or determination of arterial patency (i.e. to ensure a fair comparison, software errors will be excluded from this analysis).

We will compare the time needed for human (all, expert only, non-expert only) and software derived ASPECTS and CTA obstruction/collateral scoring separately in univariable analyses, i.e. Mann-Whitney U testing.

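### Timing study: scans are selected in equal strata but given to readers by an unstratified draw, so the case mix of the expert-only and non-expert-only comparisons is left to chance

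*SAP article*

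**What the plan says.** All of this is in the SAP article, Tertiary outcomes, 2b.

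- **Selection.** "We will select 100 NECT and 50 CTA from all RITeS cases". Eligible scans are those that the software processed successfully and on which expert and software results match. The purpose of the strata is explicit: "We will use stratified random sampling to ensure relevant scan appearances are equally represented". There are three NECT strata (no, small, and medium-large ischaemic lesion) and three CTA strata (no, proximal, and distal obstruction), "therefore ~33 cases for each NECT stratum and ~16 for each CTA stratum".
- **Readers.** "We aim to include a minimum of five expert and five non-expert readers".
- **Allocation.** "Each reader will be shown a unique random 10% selection (10 NECT and 5 CTA) of the cases". Beyond ten readers: "If more than 10 readers are recruited to the study, we will allow repeat reading of cases".
- **Analysis.** "We will compare the time needed for human (all, expert only, non-expert only) and software derived ASPECTS", and likewise CTA obstruction and collateral scoring. The method is a univariable Mann-Whitney U test, with no term for stratum.

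**The concern.** The plan controls scan appearance when it chooses the scans and drops that control when it hands them out. Elsewhere it names structured sampling where it intends it: stratified sampling for the representative sample and for this pool, cluster sampling for repeatability. The natural reading of the word random at the allocation step is therefore an unstratified draw.

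Appearance plausibly affects reading time. The same section asks for collateral scoring only where it is relevant, so a CTA without obstruction may be a shorter task. Two of the three named comparisons (expert only and non-expert only) each use one part of the pool. Their stratum mix can drift from the equal thirds that the selection was built to give, and an unstratified rank test does not correct for that. What is at stake is precision and fair reading of those two comparisons, in an outcome reported separately from the primary paper.

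**Working it through.** **Inputs** (all from section 2b): 100 NECT and 50 CTA; three strata each; at least 5 + 5 = 10 readers; 10 NECT and 5 CTA per reader. Two assumptions: stratum sizes are taken as 34/33/33 (NECT) and 17/17/16 (CTA), and unique is read as non-overlapping.

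**1. The plan's own figures.** 100/3 = 33.3 and 50/3 = 16.7, in line with the stated approximate sizes of 33 and 16. Ten per cent of 100 is 10 and of 50 is 5. Ten readers use 10 × 10 = 100 NECT and 10 × 5 = 50 CTA, so every scan is read exactly once. It follows that:

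- the all-reader comparison has exactly the planned mix;
- the expert and non-expert sets are two disjoint halves (25 and 25 CTA, 50 and 50 NECT).

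**2. Case mix of one half.** For a stratum of K scans in a pool of N, the number falling in a random half of n is hypergeometric, with mean nK/N and SD = √[n(K/N)(1 − K/N)(N − n)/(N − 1)].

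- CTA, K = 17, N = 50, n = 25: mean 8.5; SD = √(25 × 0.34 × 0.66 × 25/49) = 1.69. Mean ± 1.96 SD is 5.2 to 11.8, roughly 5 to 12.
- NECT, K = 33, N = 100, n = 50: mean 16.5; SD = √(50 × 0.33 × 0.67 × 50/99) = 2.36.

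**3. As shares.**

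| | One half v whole pool (SD) | Expert half v non-expert half (SD) |
|---|---|---|
| CTA | 1.69/25 = 6.8 points | 2 × 1.69 = 3.4 scans, 13.5 points |
| NECT | 2.36/50 = 4.7 points | 2 × 2.36 = 4.7 scans, 9.5 points |

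In 60,000 simulated random partitions, the largest stratum difference between the two halves had these values:

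- CTA: median 4 scans; at least 4 in 52% of partitions, at least 6 in 21%.
- NECT: median 5 scans; at least 6 in 46%.

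**4. Individual readers (descriptive only).** The chance that one reader's 5 CTAs miss at least one stratum, by inclusion-exclusion, is

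[2·C(33,5) + C(34,5) − 2·C(17,5) − C(16,5)] / C(50,5) = (474,672 + 278,256 − 12,376 − 4,368) / 2,118,760 = 34.7%.

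Strata of 16/16/16 give 34.5% and 16/16/18 give 35.0%, so rounding is immaterial. The same calculation for 10 NECT from 34/33/33 gives 4.1%.

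**5. Is a balanced allocation possible?** Yes. Give every reader 5 CTAs split 2/2/1, with the single falling in the first stratum for 3 readers, the second for 3 and the third for 4. The totals are 20 − 3 = 17, 20 − 3 = 17 and 20 − 4 = 16. Give every reader 10 NECT split 4/3/3, with the four falling in the first stratum for 4 readers and in each of the others for 3, for totals of 34, 33 and 33. The halves can then be CTA 9/8/8 v 8/9/8 and NECT 17/17/16 v 17/16/17. No stratum differs by more than one scan, and no reader misses a stratum.

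**The case against.** The case for leaving the plan as it stands has several parts.

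- **The stated purpose is met at pool level.** The section promises equal representation in the selected scans, not per reader or per reader group. With ten readers the pooled comparison keeps it exactly. This stands.
- **No direct expert v non-expert test is named.** Each group is compared with software. If software times come from the same scans that the group read, the case mix is identical on both sides of that test. This also stands, but the text does not say which software times are used. If all 50 CTA times are set against one group's 25, chance imbalance enters.
- **Random allocation is unbiased.** A reader might infer that reader speed is confounded with case difficulty. The documents do not support that: each half has the pool mix on average, and the cost is extra variance.
- **The one-third figure bears on no result.** A reader might infer that about a third of readers having no case from some CTA stratum damages the findings. No per-reader analysis is planned, so the figure only describes how loose the draw is, and for NECT it is 4%.
- **No effect in seconds is shown.** The documents give no reading times by stratum, so the imbalance can be sized in scans only. Restricting the pool to scans on which human and software agree limits some difficulty factors, but it does not balance strata between readers.
- **The article is condensed, and ten readers is a minimum.** Operational detail may sit elsewhere. However, the allocation rule is stated here, and it is stated without strata. With more than ten readers the halves may overlap, but no rule says which scans repeat, so balance is still not assured.

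What survives is narrow: a stated allocation rule that gives away, for two of the three comparisons, balance that could be had almost free.

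**Conclusion.** The point holds as a low-importance improvement, not as an error. At the minimum of ten readers with non-overlapping sets, the expert-only and non-expert-only comparisons rest on different halves whose stratum mix is left to chance. The noise is larger for CTA than for NECT, and the all-reader comparison is untouched. The practical weight depends on two things that the document does not give: how far reading time differs between strata, and whether software times come from all scans or only from those that the group read. Neither systematic bias nor a fault in any per-reader result is shown.

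**What to change.** 1. Replace the unstratified 10% draw with allocation within strata: 3-4 NECT and 1-2 CTA from each stratum to every reader, arranged so that the expert and non-expert sets match to within one scan per stratum. If more than ten readers join, assign repeat readings by the same rule.
2. State which software times each reader group is compared with. Either use the software times for the scans that the group read, or replace the unstratified Mann-Whitney test with a stratified rank test such as van Elteren's.

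**Cost:** a small change to the allocation procedure and a sentence or two on the test. No extra scans, readers or reading time are needed.
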